## Abstract

Diabetes Mellitus (DM) is a chronic disease characterized by abnormally uncontrolled high blood glucose level. The Risk Assessment and Management Program (RAMP) in Hong Kong has been providing long-term face-to-face follow-up to DM patients in the government out-patient clinics since 2009. However, under the current outbreak of COVID-19, these face-to-face consultations were ceased over and over again to lower the risk of disease transmission. With the advancement in technology, the recent emergence of telecare has provided an alternative to replace the conventional consultations in the clinics. Its clinical effectiveness on DM patients has also been supported by numerous studies. Yet, there is only a paucity of literatures discussing the practicality of such implementation design in the real-world settings. This study aims at studying both the effectiveness and implementation outcomes of telecare in Hong Kong DM patients. It adopts a type 2 hybrid effectiveness-implementation design. It will be conducted in seven government out-patient clinics in Hong Kong. The subjects will be randomly assigned to an intervention group or a control group when they 1) are aged 18 or above, 2) have a confirmed diagnosis of diabetes, and 3) are having regular follow-up appointment in the clinic. Subjects in the intervention group will receive a 84-week Risk Assessment and Management Program (RAMP) in an alternate telecare and face-to-face consultations mode, while the control group will receive the same program but in usual face-to-face consultation mode. RE-AIM is employed as the implementation and effectiveness outcome evaluation framework. The primary outcome measure will be HbA1c. Data will be collected pre-intervention (T1), 42-week (T2), and 84-week (T3). The study will provide effectiveness-implementation assessment of telecare mode for DM patients in Hong Kong, as an alternative or in addition to conventional face-to-face consultations. It also aimed to provide insights for the future adoption in a broader health care setting.

## Introduction

Diabetes Mellitus (DM) is a chronic, metabolic disease characterized by abnormally uncontrolled high blood glucose levels [1]. Its prevalence has risen dramatically over the past decades, reaching approximately 529 million people worldwide in 2021. It is even estimated that the figures will be doubled to 1.31 billion by 2050 [2]. In Hong Kong, 10% of the total population is affected by DM and is expected to rise to 12.8% by 2025 [3]. According to a recent study, the incidence of DM increased gradually in people aged 20 to 40 [4], implying that the DM population in Hong Kong not only becomes larger, but younger. DM can lead to a wide range of microvascular and macrovascular impacts. It is reported that 40% of patients have more than one complication such as angiopathy, retinopathy, cardiovascular diseases, and cerebrovascular diseases [5]. In addition, DM is posing a heavy burden to the healthcare systems and economy as the treatment of DM requires extensive use of medical resources. According to a study in Hong Kong, it mentioned that approximately $2 billion were spent each year as the health care cost for DM [6]. Furthermore, patients with severe complications might not be able to work. This could result in a decline in the working population, which is unfavourable to the society in the long run.

DM isn’t a disease that can be fully cured but requires a long-term follow-up and management in the community. In Hong Kong, the General Out-Patient Clinics (GOPCs) under the Hospital Authority have served millions of patients with chronic illness, including DM [7]. Since 2009, there is a program named the Risk Assessment Management Program (RAMP) that initiates in GOPCs intending to provide multidisciplinary risk assessment, complication screenings, and subsequent regular follow-up consultations to DM patients (Appendix 1 showed the RAMP workflow). Throughout these years, researchers have already proven the significant clinical effectiveness of the RAMP in terms of patients’ health outcomes such as improvement in HbA1c, blood pressure, lipid profile, and BMI [8–10]. Yet, these conventional face-to-face consultations could be time-consuming and troublesome owing to geographical issues and traveling difficulties. To illustrate, some patients might be living in far-off areas which could take them quite a lot of time to arrive at the clinic. More importantly, hospital visits greatly increase the risk of disease transmission, especially under the current COVID-19 pandemic. With the advance of science and technology, telecare consultation could be a flexible and cost-effective alternative method to continue thus consummate our support to these DM patients.

Telecare consultation is a type of virtual consultation where communication takes place between healthcare professionals and clients through telecommunication applications. In a previous study utilizing a survey design, it was found that the majority of patients who needed to contact general practices during the COVID-19 lockdown period were highly satisfied with telecare for routine consultations in terms of convenience and safety [11]. When focuses on the clinical effectiveness of telecare on DM care, a past study acknowledged that such mode has a positive impact on health indicators such as blood glucose level and lipid [12]. Moreover, a previous 5-year longitudinal study showed that using telecare as a consultation mode has led to better HbA1c, blood pressure levels, and lipid profile among DM patients than adopting the conventional face-to-face consultations [13].

While telecare consultation has its advantages over conventional consultation in managing the health outcomes of DM patients as supported by a great number of literatures, the practicality and achievability of telecare in real-world settings have yet to be explored. Possible barriers such as insufficient digital literacy, lack of access to technology, and absence of clear operational guidelines may limit the willingness of healthcare professionals to implement the intervention [14]. More importantly, economic considerations like whether the intervention meets economic principles, are all key determinants of the practicability of applying and sustaining telecare consultation in healthcare organizations. Several overseas studies with an implementation science basis have explored perceived conditions to ensure the successful implementation of telecare. For example, the majority of respondents agreed that the easiness of telecare use and its compatibility with daily life are key factors that may influence their use of telecare consultation. From a socio-economical aspect, respondents commented that it is important to have an adequate amount of financial aid to support their sustained adoption of telecare. Additionally, a safe telecare network is also crucial to protect data confidentiality as well as patient privacy [15, 16].

Implementation science provides insight for integrating new programs, such as telecare, into the healthcare system by evaluating the clinical effectiveness as well as the practicality in real-world settings. Currently, the use of telecare consultation is limited despite an outstanding telecommunication infrastructure in Hong Kong [17]. The ongoing COVID-19 pandemic creates a pressing need for telecare consultation to be integrated into the current RAMP in hopes to continue the care for DM patients. To the best of our knowledge, there are no translational researches available that explore simultaneously the effectiveness and implementation outcomes of adopting telecare model of care in a primary health care setting in Hong Kong. If this proves successful, this would be the first study locally to provide insightful understandings on the execution and maintenance of telecare consultations in not only DM care, but also in other chronic disease management in primary care settings.

## Conceptual framework

The hybrid effectiveness-implementation design of this study is guided by two models. The design of the implementation strategies is informed by the Generic Implementation Framework (GIF) [18], while the design of the effectiveness and implementation evaluations is based on the RE-AIM framework [19].

The GIF proposes that there are facilitating and hindering factors, and strategies influencing each stage of implementation process, namely, development and exploration, preparation, operation, sustainability phases [18]. Facilitating factors such as support from management level and hindering factors such as low staff engagement level may support or hamper the dissemination and implementation process of the program. The present study will therefore utilise the GIF as a foundation, and address the facilitating and hindering factors by providing appropriate implementation strategies, such as staff training and program orientation, in different stages of the implementation process.

RE-AIM is an evaluation framework to guide the effectiveness and implementation outcomes evaluation [19]. RE-AIM examines 5 dimensions: *Reach* into the target population, *Effectiveness* of the intervention, *Adoption* by the staff and setting, *Implementation* fidelity, and *Maintenance* (i.e. degree of sustainment over time). Thus, RE-AIM is ideal for structuring the proposed hybrid implementation-effectiveness evaluation. The results of these evaluations are expected to lead to more profound insights in the feasibility and translatability of the intervention, optimal training for the staff and patients, and the factors influencing the acceptance of the intervention by the target population.

## Aims

There are two aims for the present study: 1) compare the clinical effectiveness between alternate telecare and face-to-face consultations and usual face-to-face consultations in improving client outcomes (i.e. HbA1c, Body Mass Index [BMI], fasting lipid profile, medication adherence, quality of life [QoL]) and health service utilization (i.e. unscheduled attendance at general practitioners’ office, emergency department, general out-patient clinic) among DM patients, and 2) explore and identify whether an implementation strategy of alternate telecare and face-to-face consultations at general out-patient clinics is reachable to the target DM patients, adoptable to the clinic staff and clinic, implementing accurately, and sustainable in long term.

## Hypothesis

It is hypothesized that DM patients who receive alternate telecare and face-to-face consultations will have no differences in client outcomes and health service utilization outcomes compared to those who receive usual face-to-face consultations.

## Methods/design

### Study design

Hybrid effectiveness-implementation type 2 design is adopted in this study. It is a design that evaluates the effectiveness of an intervention while also considers the implementation process and factors that may influence its successful adoption and integration into real-world settings [20]. Type2 design is used when intervention in both the clinical and implementation spheres are tested simultaneously. In this study, a randomized controlled trial will be used to compare the effectiveness between alternate telecare and face-to-face consultations and usual face-to-face consultations, while both qualitative and quantitative methods will be employed to evaluate implementation strategies and determine the factors that may influence implementation process.

### Study setting, subjects and recruitment strategies

The study will be implemented in seven government out-patient clinics (GOPCs) under Hospital Authority in the New Territories West Cluster from Jan 2023 to Dec 2025. The subjects who are DM patients (either type 1 or type 2) with regular follow-up appointment in the clinic will be screened and recruited into the study if they 1) are aged 18 or above, and 2) have a confirmed diagnosis of diabetes. They will be excluded if they are 1) having dementia, 2) having unaccompanied hearing or visual loss, 3) not living in an area with Internet coverage.

Research assistants (RAs) will introduce the program to the eligible DM patients in the clinics. For those who are eligible and agreed to join, RAs will collect their signature for the consent form and baseline data. After successfully collect their data, the RAs will call the principal investigator (PI) of the research team for randomization. The PI will put the numbers (i.e. 1 = “telecare group”, 2 = “control group”) that generated from a software “Research Randomizer” into sealed envelopes and open sequentially when receive the call from RAs. A block randomization of size 8 will be employed to ensure balanced representation of the subjects in each group. The PI will provide the group list to the clinic clerk, who will then inform individual participants about their randomization results and guide them to follow the assigned delivery consultation mode. The Research Assistants (RAs), who will solely be involved in data collection, and the statistician, who will be responsible for data analysis, will be blinded to the group assignment.

### Implementation process

#### Development and exploration phase

The research team has met with the chief of service, practitioners, and the managers of the GOPCs for three times to introduce the program, discuss about the impacts of the program to the GOPCs and the DM patients, and the pros and cons. With the support of the chief of service and the staff, both parties further discuss about the strategies and logistics of adopting the telecare consultation in GOPCs. The research team has agreed to a) promote the program within the GOPCs by preparing pamphlets and posters; and b) support the program’s implementation and adoption process.

#### Preparation phase

Before commencement of the program, program orientation and training workshops have to be provided to the staff in GOPCs. The research team has introduced and explained the program, illustrated the logistics of the program, and the roles and responsibilities of each healthcare providers in the one-day workshop. Each participant also received a user guide that displays the program workflow and explains with easy text and graphic instructions how to use the telecare tool. In addition, recruitment and implementation process protocols were developed with the collaboration of the healthcare providers in the GOPCs. The Information Technology (IT) team of the Cluster will provide IT support during the whole process.

#### Operation phase

Both intervention (alternate telecare and face-to-face consultation) and control (usual face-to-face consultation) group subjects will receive DM RAMP in one of the seven GOPCs. Patients enrolled in the RAMP will undergo an initial risk assessment, which include physical examination, eye and foot assessment, laboratory testing, and complication screening. According to their conditions, the healthcare providers, including nurse, practitioners, and physiotherapists, will provide individualized diabetes education and lifestyle modification advice to the DM patients [21]. In this study, the healthcare providers for both groups will be the same to minimize the operator effect. The only difference in these two groups is the delivery model, where intervention group will receive alternate telecare and face-to-face consultations and control group will receive usual face-to-face consultations only within the 84-week study period. During this program duration, there will be a total of seven consultations for both groups as each consultation is approximately 14 weeks apart. Both groups will receive the first consultation onsite. Before the end of the first consultation, the healthcare providers will provide intervention group patients instructions on how to use HA Go, a telecommunication app that can provide virtual face-to-face service, in their next meeting. A clerk will help contact the patients one hour prior to the next consultation for rehearsal. Any technical problems will be managed in this one hour by either the clerk or the IT team.

#### Sustainability phase

The research team and the healthcare providers will discuss the implementation progress at bimonthly meetings, and if necessary, adjustment will be made. The changes will be documented throughout the process. Since the implementation of telecare consultation is still in its infancy phase for the Hospital Authority and its use is increasing, particularly during the COVID-19 pandemic, the corporate policy and guidelines of the service may be modified during the operation phase of this study.

### Sample size

Power analysis is used to estimate the sample size of the study. Based on the non-inferiority criteria of 0.4% between the two groups on the primary outcome, HbA1c, in a previous similar study [22], and the varying drop-out rates of previous studies, which ranged from 0% to 20% over a follow-up period of 1–10 years [23–26], assuming a 20% of beta error, a 0.05 of alpha level, and a drop-out rate of 20% in this study, a sample size of 350 subjects will be needed in each group, i.e. a total of 700 subjects in two groups.

### Ethics and dissemination

Ethical approval was granted from the ethics subcommittee of a university in Hong Kong. Information of significance, aims, procedures, benefits and risks will be told to all eligible subjects. Subjects will be reassured that they can refuse participation and withdraw from the study anytime without any penalty. Subjects will sign the consent form after they expressed understanding of the study. They will remain anonymous, and all data will be identified by a case number only. A telephone hotline will also be provided to the subjects for queries.

### Outcome measures

The present program will use RE-AIM as the evaluation framework.

#### Reach:

To identify how representative the enrolled patients are of the target population, the number of DM patients who are eligible, invited, excluded, and enrolled to receive telecare consultation in the GOPCs will be counted and compared to non-participants on key demographic data such as age, diabetes type and duration, and number of follow-up attendance. The RAs will also try to ask both participating and non-participating patients the reasons why they enrol or not enrol to provide further information on the reach of the program.

#### Effectiveness:

The effectiveness outcomes of the program include HbA1c, fasting lipid profile, body mass index (BMI), medication adherence, quality of life (QoL), and health service utilization. The primary effectiveness outcome of this study is the HbA1c level. HbA1c is a standard assessment of glycemia and refers to the mean blood glucose levels over the previous 2 to 3 months [27]. Fasting lipid profile includes cholesterol level, and high- and low-density lipoprotein. Similar to HbA1c, the fasting lipid profile will be drawn from patients’ blood when the patient has onsite consultation. The results can be extracted from the hospital database. BMI will be measured each time during GOPC admission by dividing weight in kilograms by height in meters^2^. Medication adherence will be measured by adherence to refills and medication scale [28]. This 4-point Likert scale has scores range from 12 to 48, with lower scores representing better medication adherence. The scale has demonstrated high internal consistency, with a Cronbach’s alpha of 0.81 [28]. Quality of life will be evaluated by the version 2 of the 12-item Short Form Health Survey [29]. The scale measures various aspects of physical and mental health from which physical and mental component scores can be summed. It has been widely used in Chinese diabetic patients with good validity and reliability [30,31]. The outcomes of health services utilisation include the total number of unscheduled visits to general out-patient departments, general practitioners (GP), emergency departments, and hospitals, and the total health service attendance. The information will be extracted from the hospital database, except for GP visits, which will be reported by the subjects.

Background demographic data will be collected to compare the baseline differences between the two groups. They include age, gender, marital status, education, work status, years of using a smartphone, financial status, family living in the same household, caretaking support, diabetes type and duration, date of first follow-up, number of referrals, professionals to whom the patient is referred.

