### Data collection

Data will be collected at three time-intervals, baseline pre-intervention (T1), 42 weeks (T2), and 84 weeks after the interventions begin (T3). The RAs, who are blinded to group allocation and not involved in interventions, will collect the data in the GOPCs in T1, and *via* telephone call in T2 and T3. They will be tested on inter-rater reliability to ensure data quality. Five percent of the data will also be randomly selected for independent review. Participants will receive a HK$ 50 coupon as a token of appreciation for their time commitment and to help cover transportation costs upon completion of the T3 data collection.

Semi-structured interviews will be carried out in T3 by research team members. A one-time in-depth focus group interview allows the research team to understand the group dynamics where different opinions from persons can be explored. During the interview, participants will be asked questions such as "What is your experience with the telecare consultation?" and "What aspects of the intervention program do you like or dislike?" At each time point, separated interviews will be conducted to the same group of people including (1) GOPC manager, (2) clinic healthcare providers (i.e. doctor, nurse), and (3) 64 (20%) of the patients in telecare group.

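### The week-42 assessment (T2) falls on a telecare consultation in the intervention arm, and the article states no source of week-42 HbA1c, lipids or BMI for that arm

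*Protocol article*

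**What the plan says.** All references are to the protocol article.

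- **Visit schedule (Operation phase).** "there will be a total of seven consultations for both groups as each consultation is approximately 14 weeks apart". On the mode of the opening visit, the section says: "Both groups will receive the first consultation onsite". At that first visit the intervention patients are given "instructions on how to use HA Go, a telecommunication app that can provide virtual face-to-face service, in their next meeting", so their second consultation is by telecare. Over the whole programme, "intervention group will receive alternate telecare and face-to-face consultations and control group will receive usual face-to-face consultations only within the 84-week study period".
- **Measurement (Effectiveness).** "Similar to HbA1c, the fasting lipid profile will be drawn from patients’ blood when the patient has onsite consultation". The results are then taken from the hospital database. "BMI will be measured each time during GOPC admission".
- **Assessment times (Data collection).** These are "baseline pre-intervention (T1), 42 weeks (T2), and 84 weeks after the interventions begin (T3"). The research assistants collect their T2 and T3 data by telephone.
- **Promised comparison (Discussion).** BMI, blood glucose, lipids and HbA1c are to be measured and compared at three time points.
- **Primary outcome and test (Effectiveness; Data analysis).** HbA1c is primary. It is tested by a t-test against a margin of 0.4% with a one-sided 95% bound. The time point of that test is not given.

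**The concern.** The visit pattern, the sampling rule and the assessment week are each stated, and together they do not fit. At T2 every control patient on schedule is in the clinic and every intervention patient on schedule is on a video call. Blood and weight are tied to being in the clinic. The article states no separate draw or weighing for the telecare arm at week 42, and no rule for assigning another visit's result to T2.

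Three things could happen in practice, none of them a fair T2 comparison:

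- The intervention values are missing.
- Values from week 28 or week 56 stand in for week 42, so the arms are measured at different times and any shared time trend appears as an arm difference.
- Week-42 values exist only for intervention patients who happened to attend onsite. The Maintenance section foresees patients asking to change mode, and such patients are a self-selected group.

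Data not collected alike in both arms at T2 cannot be recovered later by analysis.

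**Working it through.** **1. Reproduce the stated programme length.** Inputs from Operation phase: 7 consultations, 14 weeks apart. Consultation k falls at week 14 × (k − 1). The last is at 14 × 6 = 84 weeks, which matches the stated 84-week programme.

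**2. Assign the modes.** The first consultation is onsite, the second is telecare in the intervention arm, and the modes then alternate.

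| Consultation | Week | Intervention | Control | Assessment |
|---|---|---|---|---|
| 1 | 0 | onsite | onsite | T1 |
| 2 | 14 | telecare | onsite | |
| 3 | 28 | onsite | onsite | |
| 4 | 42 | telecare | onsite | T2 |
| 5 | 56 | onsite | onsite | |
| 6 | 70 | telecare | onsite | |
| 7 | 84 | onsite | onsite | T3 |

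The spacing is only approximate, so I tried 13 and 15 weeks. Consultation 4 then falls at week 39 or 45 and is still telecare.

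**3. Distance to the nearest intervention-arm draw.** Weeks 28 and 56 are each 14 weeks from week 42. The Effectiveness section puts the HbA1c look-back at 2 to 3 months, about 9 to 13 weeks. With the longer figure, a week-42 value reflects roughly weeks 29–42, a week-28 value weeks 15–28, and a week-56 value weeks 43–56. On schedule these periods do not overlap.

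**4. Illustration of size.** This applies only if neighbouring values are substituted and the non-inferiority test is run at T2. The article gives no figure for drift. I assume a common drift of 0 to 0.1 HbA1c point per 14 weeks, which biases the T2 difference by the same amount, b.

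- Standard error implied by the plan (margin 0.4, one-sided 5%, power 80%, true difference zero): SE = 0.4 / (1.645 + 0.842) = 0.161.
- False non-inferiority rate when the bias favours telecare: Φ(b/SE − 1.645).
- Power when the bias goes against telecare: Φ((0.4 − b)/SE − 1.645).

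| Assumed drift b | False non-inferiority rate | Power |
|---|---|---|
| 0 | 5% | 80% |
| 0.05 | 9% | 70% |
| 0.1 | 15% | 59% |

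The two columns are alternatives: which one applies depends on the direction of the drift and on whether week 28 or week 56 is substituted.

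**The case against.** The strongest reply has four parts.

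- **The article does not say blood is drawn only onsite.** That is correct. Results come from the hospital database, laboratory testing is part of the programme, and the workflow appendix is not shown. A fuller protocol may hold a separate arrangement. So the defensible statement is that no week-42 source is stated, not that none exists. The published text still sets a sampling rule, a visit pattern and an assessment week that conflict, and it needs correcting.
- **Telephone collection at T2 proves nothing about blood.** This also stands. The research assistants telephone at T3 too, when both arms are onsite. The point rests on the visit pattern and the sampling rule alone.
- **The primary analysis may be untouched.** A reader might infer that the primary non-inferiority result is compromised, especially as the Maintenance section labels the week-84 measurement a sustainability outcome and so seems to leave week 42 for effectiveness. The document does not support that conclusion. Data analysis names no time point, and week 84 is onsite in both arms. If week 84 is used, the primary comparison is intact.
- **The error rates rest on an assumed drift.** They do. At zero drift the bias vanishes, and if T2 values are simply missing there is no T2 contrast to bias. The non-overlap of look-back periods is also narrow (13 weeks against 14), so modest visit slippage would give some overlap.

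**Conclusion.** The inconsistency is real and follows from the article's own schedule without any outside assumption. For patients on schedule, week 42 offers an onsite draw and weighing to all of the control arm and none of the intervention arm, and the article states no other route. The T2 comparison of HbA1c, lipids and BMI cannot be carried out as described.

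Its reach is limited to those outcomes at T2. It extends to the primary test only if that test uses T2, which is left open. The figures of up to about 15% false non-inferiority or down to about 59% power are illustrative. They require substituted values, a test at T2, and a drift of 0.1 point per 14 weeks that the documents do not give.

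**What to change.** Leave the consultations as they are and reconcile the Operation phase, Effectiveness, Data collection and Discussion sections:

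1. Take T2 HbA1c, lipids and BMI in both arms at a consultation that is onsite in both, week 28 or week 56. State which, with a common window.
2. State that a week-42 control value will not be compared with a week-28 or week-56 intervention value.
3. Name week 84, onsite in both arms, as the time point of the primary HbA1c non-inferiority test.

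**Cost.** This is a wording change with no extra attendance. T2 laboratory and BMI data are no longer at the exact midpoint, and telecare exposure at T2 depends on the choice: week 28 follows one telecare consultation (week 14), week 56 follows two (weeks 14 and 42). Week 28 therefore gives the weaker contrast.

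**Alternative.** A dedicated draw and weighing around week 42 in both arms keeps the midpoint. It needs an extra attendance in the telecare arm, which partly undoes the delivery mode under test, so it is not the cheap option.
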